## Abstract

**Introduction:**

Incontinence is commonly experienced by adults who receive care support in a residential facility or in their own home. These individuals are at risk of developing incontinence‐associated dermatitis (IAD), which is caused by prolonged and repeated exposure of the skin to urine or faeces. An IAD manual was developed providing an evidence-based clinical algorithm and an e-learning training programme for the prevention and treatment of IAD. The aim of the study is to establish the feasibility of conducting a definitive trial to examine the clinical and cost-effectiveness of the IAD manual. The objectives are to assess recruitment and attrition rates, acceptability of the IAD manual and intervention fidelity.

**Methods and analysis:**

A feasibility cluster randomised controlled trial will be conducted in residential nursing homes and in the homes of people receiving formal care support in London and Hampshire, England. A total of six clusters including n=248 participants who are incontinent of urine, or faeces will be included. At each intervention site, care staff will be trained to implement the IAD manual over a 6-month period. Quantitative outcomes include IAD incidence and severity, IAD-related pain, satisfaction with care and mental health. A qualitative evaluation of care staff and care receivers’ experiences of participation will be conducted. Rates and proportions of each feasibility outcome will be described informing the sample size estimation for a definitive cluster randomised controlled trial. A thematic analysis of the qualitative data will be guided by a logic model detailing potential factors impacting on both the study methodology and adoption of the IAD manual into routine care.

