## Introduction

### Background

 Incontinence‐associated dermatitis (IAD) is an irritant contact dermatitis caused by prolonged and repeated exposure of the skin to urine, faeces, or both.^1^ It is characterised by erythema, maceration and in some cases skin loss, swelling and bullae.^2^ IAD can be painful and is often associated with itch. If not prevented or treated, IAD can lead to secondary infections, increased risk of pressure ulcer development and morbidity.^3^ This can impact quality of life, such as reduced social activities and a greater dependence on formal and informal carers.

Prevalence and incidence estimates for IAD among people receiving long-term care are few and variable with no reliable UK estimates available. In a long-term care facility in the USA, IAD prevalence of 23% on admission with 8% incidence (in those without IAD at admission) was reported over 12 weeks.^4^ IAD prevalence among those with incontinence could well be higher in the community (41%)^5^ although the proportion of people experiencing incontinence is lower (~35%)^6^ than in nursing care homes (43%–77%—mean 58%).^7^ This may be due to different skincare routines or lack of support with personal hygiene at the time it is needed in the community. Among community-dwelling adults with faecal incontinence, a prevalence of IAD of 51% has been reported.^8^ Recent studies in nursing care homes in Germany estimate the point prevalence of IAD at 20.1%^9^ and IAD incidence of 23%–26% within 6 months.^10^ In the USA, the incidence of IAD was found to be 5.5% over 14 days, among nursing home residents^11^ and as high as 30% over 1 month in Belgian nursing homes.^12^

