## Methods and analysis

### Trial design and setting

A two-arm feasibility cluster randomised controlled trial (RCT) will be conducted for 6 months. It will take place in four care homes (two in region A and two in region B) and two home care agencies (one in region A and one in region B). Region A comprises the largely urban setting of London, UK and region B denotes a more rural area and relatively smaller cities of Hampshire, UK. The term, care home, describes both nursing and residential care homes where people live to receive support with personal and social care. Home care agencies are professional organisations that provide personal and social care to adults living in their own homes. These are settings and services most likely to provide care to people with incontinence.

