### Recruitment

Our PPI panel and research team networks will advise on cluster sites to invite into the study. Forty-eight people with urinary and/or faecal incontinence (with or without IAD) will be recruited per study site to take part in the feasibility RCT. Researchers will liaise with care staff managers at each study site and ask them to identify potential participants they know are incontinent. If someone is not capable of deciding if they want to take part, a personal consultee will be sought (ie, nominated next of kin or whoever is nominated as the first point of contact in the person’s records). If it is not possible to either identify or contact that person within 2 weeks, then a nominated consultee independent of the project such as the person’s GP or nominated care manager will be approached. If no response from the nominated consultee is received after 2 weeks, then the person will not be included in the study. If a personal consultee is identified after a nominated consultee has signed a declaration, then the participant will be reconsented under the personal consultee process.

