### Sample size

Two care agencies and four large care homes each with approximately 100 residential and nursing care beds will be recruited and randomised as a cluster (one home care agency and two care homes in region A, with equivalents in region B). An IAD prevalence of 30% would provide 180 people with IAD (from 600) and would be sufficient to estimate recruitment and retention rates (80% recruitment, n=144) with a maximum margin of error of approximately ±7%. Forty-eight individual participants with incontinence (with or without IAD) will be recruited per site, anticipating a mean of 58 people with incontinence per 100 beds, and 30 with IAD per 100 beds.^7 12^ An overview of the planned participant flow is shown in figure 2.

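### The abstract's total of 248 participants does not agree with 48 per site at six sites, which gives 288

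*Protocol article*

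**What the plan says.** The abstract (Methods and analysis) gives the size of the trial as follows: "A total of six clusters including n=248 participants who are incontinent of urine, or faeces will be included".

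The body gives a per-site figure, twice. Under Recruitment: "Forty-eight people with urinary and/or faecal incontinence (with or without IAD) will be recruited per study site to take part in the feasibility RCT". Under Sample size: "Forty-eight individual participants with incontinence (with or without IAD) will be recruited per site".

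Trial design and setting fixes the number of sites at six: "It will take place in four care homes (two in region A and two in region B) and two home care agencies".

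The Sample size section supports 48 by expecting a mean of 58 incontinent people per 100 beds. It describes the sites in one sentence, "Two care agencies and four large care homes each with approximately 100 residential and nursing care beds will be recruited", and then works from a pool of 600: "An IAD prevalence of 30% would provide 180 people with IAD (from 600" in total). In the Background, 58% is the mean for nursing care homes. For the community, the same paragraph says that "the proportion of people experiencing incontinence is lower (~35" per cent).

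**The concern.** The article contains two planned sample sizes for the same population, people with incontinence with or without IAD, at the same stage, recruitment. A reader of the abstract would take the plan to be 248. A reader of the methods would take it to be 288. Enrolling 248 would be the full plan on one reading and 86% of it on the other.

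The number also matters as a description of cluster size. The study is meant to inform the design of a definitive cluster trial, and a reader needs to know how many participants were planned per home and per agency. The single figure of 48 covers both settings but is supported only by a care-home incontinence rate, although the article itself reports a lower rate in the community.

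**Working it through.** **Inputs**
- Stated total: 248 (Abstract).
- Sites: 4 care homes + 2 home care agencies = 6 (Trial design and setting).
- Target per site: 48 (Recruitment; Sample size).
- Incontinence: 58 per 100 beds (Sample size); about 35% in the community (Background).
- Pool: 600 people; IAD prevalence 30%; recruitment 80%, n=144; margin about ±7% (Sample size).

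**1. The total**
- Sites × target per site = 6 × 48 = 288.
- Gap: 288 − 248 = 40; 40/288 = 13.9%; 40/248 = 16.1%; 248/288 = 86.1%.
- 248/6 = 41.3, which is not a whole number, so no equal target per site gives 248.

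**2. Whether an obvious adjustment links the two**
- 80% of 288 = 230.4.
- 90% of 288 = 259.2.
- Five sites: 5 × 48 = 240.
- 80% of 58 at six sites: 6 × 58 × 0.8 = 278.4.

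None gives 248, and the text states no attrition allowance, cluster adjustment or separate agency target that would.

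**3. The target of 48 by setting**
- Care home: 48/58 = 82.8% of the expected incontinent residents. This is attainable.
- Agency: a pool of 600 over six sites implies 600/6 = 100 people each. If 35% are incontinent, 0.35 × 100 = 35 are eligible, and 35 < 48.
- Clients needed for 48 eligible people at 35% with every one recruited: 48/0.35 = 137.1, so 138.

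**4. What does not depend on the total**
- 600 × 0.30 = 180 and 180 × 0.80 = 144, as the plan states.
- Margin = 1.96 × √(p(1−p)/n). With p=0.5 and n=180 it is ±7.3%; with p=0.8 and n=144 it is ±6.5%. Both agree with about ±7%.
- Neither 248 nor 288 enters this calculation.
- The thresholds under Prevalence and incidence (at least 10% IAD prevalence in at least 3 sites, 70% screened, 70% completion of outcome measures by care staff) use neither total, nor 48.

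**The case against.** The strongest reply is that little depends on the answer. No significance testing is planned, the precision statement rests on 180 and 144, and no feasibility threshold is expressed against a total. The first primary objective is to determine how many people are eligible and agree, without a target. That stands, and it limits the consequence. It does not remove the contradiction.

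A second reply is that the participant-flow figure, which cannot be seen here, may show a split by setting. That is possible, but the two sections that state 48 do so for every site, so the text would still need correcting.

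A reader might also infer several stronger points that the documents do not support:

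- **That 48 is unreachable at an agency.** The 35% is a background figure for the community that the sample size section does not use. It may not describe agency clients, since Trial design and setting places these services among those most likely to care for people with incontinence. An agency size of about 100 is only implied by the pool of 600, because an agency has no beds. With 138 or more clients, 48 is arithmetically possible even at 35%.
- **That 48 also fails in care homes.** Applying 80% recruitment to 58 gives 46.4, just under 48. But the plan applies its 80% to the 180 people with IAD, not to all incontinent people.
- **That 248 comes from 28 per agency.** It is true that 4 × 48 + 2 × 28 = 248, with 28 = 0.8 × 35. But this uses 83% recruitment in homes and 80% in agencies. A consistent 80% gives 4 × 46.4 + 2 × 28 = 241.6. A one-digit slip between 248 and 288 is at least as plausible.
- **That recruitment will be judged against this total, so that agencies would appear to fail.** The plan contains no such test.

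**Conclusion.** The contradiction between 248 and 288 is certain. It follows from multiplication of figures in the current text, it amounts to 40 participants, and no visible rule resolves it. The documents do not show which total is intended, so 288 should not be assumed to be the right one.

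The point about the agencies is secondary and rests on two assumptions: about 100 clients per agency, and the background 35% applying to those clients. If both hold, about 35 people would be eligible against a target of 48. What stands without these assumptions is narrower: the sample size section uses a care-home incontinence rate for all six sites, although the Background reports a lower community rate.

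The effect is on the clarity of the plan. The ±7% precision, the feasibility thresholds and the planned analyses do not change.

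**What to change.** The sponsor should confirm the intended total and state the same figure in the Abstract, Recruitment, Sample size and the participant-flow figure. The Sample size section should show how the total is built up by setting, with the number of sites and the target per site for care homes and for agencies.

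The agency target should be derived from an incontinence rate suited to agency clients and from the expected number of clients per agency, both stated. The description of site size in beds should be reworded so that it applies to care homes only.

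The cost is a wording correction. No extra participants are needed if 248 is intended. If 288 is intended, the abstract changes and the article should show that each agency is large enough to supply its share.

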**Ethics and dissemination:**

The study received the approval of the Queens Square Ethics Committee Health Research Authority 23/LO/036, (Project ID 296167). Results will be disseminated through peer-reviewed open-access journals and international conferences

**Trial registration number:**

ISRCTN70866724.

STRENGTHS AND LIMITATIONS OF THIS STUDYThe trial procedures and intervention have been developed from current evidence and logic modelling with sustained involvement from people with lived experience, informal carers and care staff who manage skincare for people at risk/with incontinence‐associated dermatitis (IAD).A mixed methods approach will be used to investigate the feasibility and acceptability of both the intervention and the planned study procedures.The study is embedded within the context of care home and home care agency provision enabling an understanding of how the intervention may be implemented in community and social care settings.The study design is a cluster randomised controlled trial to minimise potential bias and contamination.The study will be conducted in two regions in England which may limit the generalisability of the study findings.

## Introduction

### Background

 Incontinence‐associated dermatitis (IAD) is an irritant contact dermatitis caused by prolonged and repeated exposure of the skin to urine, faeces, or both.^1^ It is characterised by erythema, maceration and in some cases skin loss, swelling and bullae.^2^ IAD can be painful and is often associated with itch. If not prevented or treated, IAD can lead to secondary infections, increased risk of pressure ulcer development and morbidity.^3^ This can impact quality of life, such as reduced social activities and a greater dependence on formal and informal carers.

Prevalence and incidence estimates for IAD among people receiving long-term care are few and variable with no reliable UK estimates available. In a long-term care facility in the USA, IAD prevalence of 23% on admission with 8% incidence (in those without IAD at admission) was reported over 12 weeks.^4^ IAD prevalence among those with incontinence could well be higher in the community (41%)^5^ although the proportion of people experiencing incontinence is lower (~35%)^6^ than in nursing care homes (43%–77%—mean 58%).^7^ This may be due to different skincare routines or lack of support with personal hygiene at the time it is needed in the community. Among community-dwelling adults with faecal incontinence, a prevalence of IAD of 51% has been reported.^8^ Recent studies in nursing care homes in Germany estimate the point prevalence of IAD at 20.1%^9^ and IAD incidence of 23%–26% within 6 months.^10^ In the USA, the incidence of IAD was found to be 5.5% over 14 days, among nursing home residents^11^ and as high as 30% over 1 month in Belgian nursing homes.^12^

Alongside continence promotion and appropriate use of pads and appliances,^13 14^ effective prevention and treatment includes skin cleansing and application of skin protectants.^1 15 16^ Skin protectant products comprise different formulations and ingredients such as petrolatum, zinc oxide, dimethicone or other film-forming molecules.^1 17^ Cleansers contain surface active agents, which help to dissolve the fat-soluble components in water.^18^ The odds of developing IAD if preventative measures are used are almost half (46%) the odds if they are not^11^ and when skincare regimes are implemented, costs might be reduced.^19 20^ The products and procedures for both prevention and treatment are similar^1 17^ and there are numerous options on the market, including prescription and ‘over the counter’ products. However, there is a lack of high-quality clinical trials meaning recommendations are based on low-quality evidence and expert opinion.^21^ Clear guidance is not easily available and public involvement has told us that the use of skin protectants in care homes is variable.

Although skin health can be improved using tailored and evidence-based skincare routines,^9^ nurses find it difficult to differentiate between IAD and other conditions such as pressure ulcers.^22 23^ Nurses are, however, knowledgeable about how IAD is caused but less able to diagnose and make evidence-based prevention and treatment decisions.^24 25^ Nurses’ ability to recognise IAD has been shown to improve through training,^23^ indicating the importance of continuous professional development for the prevention and treatment of IAD. Educational interventions to improve nurses’ management of IAD have taken place largely in hospital settings^24 26 27^ but are lacking in the community where the prevalence is high and unregistered care workers and informal carers provide skincare as well as registered nurses.

To meet the need for accessible, evidence-based clinical guidance, a manualised package of care for the prevention and treatment of IAD was codesigned with people with experience of IAD, informal carers and care staff. This intervention (to be referred to as the IAD manual in this article) is comprised of protocols in the form of an interactive treatment algorithm supported by an e-learning training programme. The IAD manual involves several interacting components (see figure 1) and as such meets the criteria for a complex intervention.^28^ Evaluation of interventions that are complex is often associated with problems of acceptability and lack of understanding of the barriers to implementation or stakeholders’ willingness to participate in research (Craig *et al*). To ensure full consideration of contextual factors, the Medical Research Council framework for the design and evaluation of complex interventions will be followed.^28 29^ The IAD manual is underpinned by a previous Cochrane review^1^ and an international consensus statement.^17^ The Cochrane review, which has been updated and is currently undergoing peer review, supports a structured skincare regime for the prevention and treatment of IAD. It includes two key steps: (1) skin cleansing to remove urine/faeces and (2) application of a skin protectant/leave-on product to avoid or minimise exposure to moisture and irritants.^16 30^ No-rinse or pH neutral skin cleansers or incontinence wipes are recommended, and traditional soap should be avoided.^1^ Although structured skincare algorithms have been proposed,^10^ this is the first specifically focusing on IAD prevention and treatment in community and social care settings.

**Figure 1 F1:**
[figure not shown]
Logic model—PREVENT-IAD manual. PREVENT-IAD, PREVENTion and treatment of incontinence-associated dermatitis through a codesigned manual.

### Objectives

The overall aim of this study is to evaluate the feasibility of implementing an IAD manual in community and social care settings.

The primary objectives are to:

Determine the number of adults who are eligible and agree to participate.Assess the recruitment procedures at study sites.Determine retention and attrition rates for intervention and control arms of the study.Assess the relevance and acceptability of the intervention, data collection methods and outcome measures.Evaluate intervention fidelity.

Secondary objectives are to:

Assess the incidence of IAD, IAD-related pain; satisfaction with care for the prevention and treatment of IAD and anxiety and depression.

## Methods and analysis

### Trial design and setting

A two-arm feasibility cluster randomised controlled trial (RCT) will be conducted for 6 months. It will take place in four care homes (two in region A and two in region B) and two home care agencies (one in region A and one in region B). Region A comprises the largely urban setting of London, UK and region B denotes a more rural area and relatively smaller cities of Hampshire, UK. The term, care home, describes both nursing and residential care homes where people live to receive support with personal and social care. Home care agencies are professional organisations that provide personal and social care to adults living in their own homes. These are settings and services most likely to provide care to people with incontinence.

### Eligibility criteria

Care receivers will meet inclusion criteria if they have: (1) urinary and/or faecal incontinence with or without IAD and are residents of a care home (providing nursing and/or residential care) or (2) have with urinary/faecal incontinence with or without IAD and are receiving care from a home care agency and are (3) capable of giving valid consent, that is, voluntary and informed, or declaration by personal or nominated consultee where they lack capacity to give informed consent as defined by the UK Mental Capacity Act 2005.^31^ The UK Mental Capacity Act (2005) states an individual needs to understand the research procedures and be able to decide if they want to take part, to be assessed as having capacity to consent. If capacity to consent is unclear, clinical members of the research team will seek the opinion of family members and care managers to ascertain capacity of the potential participant. Care home residents and people living at home who receive care and are continent of both urine and faeces will not be eligible.Named relatives or significant others of care home residents and people receiving care from a home care agency who have incontinence, with or without IAD, will be eligible to take part in the qualitative interviews.Care staff who provide incontinence care for people in care homes or their own home (ie, registered nurses, care assistants) will be eligible to participate in the study. Care managers will also be invited to take part to provide information about the trial methodology and the intervention. Other personnel employed at the care home who are undertaking work experience, volunteers or short-term agency staff or are not involved in direct continence care will not be considered eligible.

### Public and patient involvement

People living with IAD and informal carers have been involved in the development of the PREVENT IAD manual (intervention) and design of the feasibility study. The study’s patient and public involvement (PPI) panel comprises three members, including a PPI coapplicant who has experience of IAD and two informal carers of family members with IAD. They have been centrally involved in determining study objectives and design. There are also two representatives from Bladder Health UK who are on the Project Steering Group. Specific PPI contributions are detailed in the relevant sections of the article below.

